## Abstract

**Introduction::**

Post-stroke cognitive impairment (PSCI), which has a high morbidity, is closely associated with the recurrence and rehabilitation of ischemic stroke. There are 2 different stages of PSCI, including post-stroke cognitive impairment with no dementia (PSCIND) and post-stroke dementia (PSD). The latter has a significantly higher mortality rate than the previous one. Therefore, preventing the onset of PSD is of vital importance. However, there is no unequivocally effective prevention or treatment for PSCI, except intensive secondary prevention of stroke. The primary aim of this protocol is to explore whether acupuncture can improve cognitive function of patients with PSCIND and reduce the chances of developing PSD. On this bias, we also want to explore its possible mechanisms.

**Methods and analysis::**

A prospective, multicenter, large sample, randomized controlled trial will be conducted. A total of 360 eligible patients will be recruited from 5 different hospitals and randomly allocated into the acupuncture group (AG), sham acupuncture group (NAG), and waiting-list group (WLG) in a 1:1:1 ratio. The intervention period of NAG and AG will last 3 months (30 minutes per day, 3 times per week). Primary and secondary outcomes will be measured at baseline, 12 weeks (at the end of the intervention), 24 weeks (after the 12-week follow-up period), and 36 weeks (after the 24-week follow-up period). Resting-state and task-state functional MRI will be conducted at baseline and 12 weeks.

**Ethics and dissemination::**

The ethic committee of First Teaching Hospital of University of Traditional Chinese Medicine approved the study. Study results will be first informed to each participant and later disseminated to researchers, and the general public through courses, presentations and the internet, regardless of the magnitude or direction of effect. The results will also be documented in a published peer-reviewed academic journal.

**Registration::**

We have registered at ClinicalTrials.gov(ChiCTR2000033801).

## Introduction

1

Stroke is one of the leading causes of death and disability in the world.^[1,2]^ A study^[3]^ shows that even minor stroke can influence activities of daily living (ADLs), cognitive function, and quality of life. This brought great financial burden to patients and society.^[4,5]^ Stroke survivors are at an increased risk of developing cognitive impairment.^[6]^ Post-stroke cognitive impairment (PSCI) has a high morbidity; a recent follow-up study^[7]^ shows that prevalence of PSCI was 61% among 10-year stroke survivors. PSCI is also associated with recurrence of ischemic stroke in high-risk patients during adequate medical therapy including antiplatelet therapy. The lowest tertile of Mini-mental State Examination (MMSE) score (0∼23) was independently associated with the risk of recurrent ischemic stroke.^[8]^

PSCI contains 2 different degrees of cognitive impairment, including post-stroke cognitive impairment with no dementia (PSCIND) and post-stroke dementia (PSD). In America, a study on 212 subjects from the Framingham Study suggested that 19.3% of cases developed into the dementia in 10 years after stroke.^[9]^ In order to prevent the onset of dementia, early diagnosis and intervention of PSCIND is vitally important. The AHA/ASA Guidelines for adult stroke rehabilitation and recovery (2016) recommends that all clinical stroke patients should get screening of cognitive status before leaving hospital.^[10]^ However, there is no unequivocally effective treatment for PSCI patience. So far, the best way to prevent PSD is to prevent stroke recurrence and severity by using optimal acute treatment and intensive secondary prevention.^[11]^ Cholinesterase inhibitors commonly used in Alzheimer disease (AD), such as donepezil, also have positive effects on PSCI patience.^[12–14]^ However, the uncertainty on the global and daily function makes it difficult to evaluate the worth of the drugs on clinic.^[15]^ Therefore, it is of vital importance to explore effectively treatment to slow or stop disease progression. In recent years, studies^[16]^ have shown that acupuncture combined medication, such as donepezil or nimodipine, is more beneficial to cognitive function of PSCI patience. But there are few studies that focus on the individual effects of acupuncture on PSCI.

Therefore, the primary aim of this study is to explore whether acupuncture can improve cognitive function of patients with PSCIND and reduce the chances of developing PSD. Furthermore, we also want to explore its possible mechanisms. Recent studies show that PSCI is a result of mixed damage mechanisms, but the ongoing ischemic vascular processes may be the main mechanism.^[17]^ However, there is still a lack of studies on the mechanism of acupuncture on improving cognitive function. Therefore, in this parallel study, we want to not only probe into the effect of acupuncture, but also explore its mechanism by using function-MRI and analysis of amyloid beta (Aβ).

## Methods and analysis

2

### Objective

2.1

The aim of this study was to evaluate the efficacy of acupuncture treatment on improving cognitive function, ADLs, mental state, and quality of life for PSCIND patients, and also explore its possible mechanisms.

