### Outcome assessment

3.5

In this trail, most primary and secondary outcomes will be measured at baseline, the end of intervention(12weeks), after an additional 12-week follow-up period (24 weeks) and after an additional 24-week follow-up period (36 weeks). Amyloid-β and fMRI will be measured at baseline and the end of intervention. A summary of all the measures in the trial is summarized in Table 3.

**Table 3 T3:** Outcome measurements at each timepoint.

Study period	Enrolment	Intervention	Follow-up	
STUDY TIMES	The first time	The second time	The third time	The fourth time
TIME POINT	−3d-0	12 wks ± 3d	24 wks ± 3 d	36 wks ± 3d
MoCA	×	×	×	×
MMSE	×	×	×	×
CDR	×	×	×	×
NPI	×	×	×	×
WHOQOL-BREF	×	×	×	×
FAQ	×	×	×	×
β-Amyloid	×	×		
Adverse Reaction/Event		×	×	×
Vital signs	×	×	×	×
Recurrence		×	×	×
Using drugs	×	×	×	×
Laboratory examination	×	×		

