### Primary outcome

3.6

The primary outcome of this study is the cognitive function and incidence of PSD.

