### Instrumental activities of daily living (IADL)

4.1

Compared with basic ADLs, functional changes are noted earlier in the dementia process with instrumental activities of daily living (IADLs).^[34]^ We will use the Functional Activities Questionnaire (FAQ), which has a wide application to measure the IADLs. The target population of FAQ includes adults with normal cognition, MCI, as well as mild, moderate, and advanced dementia.^[35]^

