### Neuropsychiatric inventory (NPI)

4.2

The evaluation of neuropsychiatric symptoms is an important part of dementia diagnosis and management.^[36]^ The 12-item version of neuropsychiatric inventory (NPI) will be used in this trial. Compared with the original NPI with 10 items, this version added the elements of sleep/nighttime, behavior disturbances, and appetite/eating disturbances.^[37]^

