### Sample size and statistical methods

7.5

The sample size calculation is based on the improvement of Montreal cognitive assessment scale (MoCA) scores, which has a higher sensitivity than MMSE for MCI.^[7]^ According to the similar published articles,^[40]^ the mean difference in MoCA scores between AG and control group (CG) is 1.5, with a standard deviation of 1.13 in AG and 1.20 in CG. According to our previous study, acupuncture treatment can probably improve the MoCA by 0.6 on average compared with control group. Considering a 1-sided significance level of 0.025 and power of 95%, 95 participants are required for each group, as calculated by PASS 11 software. To minimize attrition bias, we assumed the dropout rate of 20%, making it necessary to include at least 357 participants with a 1:1:1 group allocation rate. We plan to enroll 360 participants in total.

Continuous variables are presented as mean (SD) if they obey normal distribution, and paired-sample *t* test will be used in intragroup comparison; if they are not normal distribution, median (quartile interval) [M(IQR)] will present them, and Wilcoxon rank sum test will be used in intra-group comparison; Variance analysis will be used for comparison between groups which is consistent with the normal distribution and homogeneity of variance; if not, then Mann–Whitney *U* test will be used. Group comparisons will then be undertaken using χ^2^ tests for categorical characteristics. Two-sided *P* < .05 represents statistical significance for all the analyses.

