## Discussion

8

By reason of the high prevalence of PSCIND and high social acceptability of acupuncture in China, we have the advantage on conducting large-sample research. This protocol design also has additional strengths. First, as far as we know, we are the first randomized controlled trial to study if acupuncture has efficacy on preventing PSCIND progressing to PSD; second, avoiding false increase of patients’ cognitive-function test results caused by multiple use of same scale. We measure the cognitive function with different version of MoCA, including 7.1, 7.2, 7.3, and basic of MoCA; third, multicenter. Our trial will be conducted in 5 inpatient and outpatient stroke rehabilitation units of different cities, which can ensure the sample representativeness. Fourth, a 12-week intervention and 24-week follow-up assessment can provide reliable long-term effect evidence for acupuncture on improving cognitive function, mental state, and quality of life for PSCIND patients.

On the contrary, this protocol design also has limitations, which are as follows. There could be a very few overlaps exists between early stage of AD and PSCIND in our participants. Fifty-six percent of all demented cases are the patients who suffer from AD with stroke.^[41]^ A Study also shows that the atherosclerosis, which is one of the common causes of stroke, may also have effects on the pathogenesis of AD.^[42]^ We can see that the inner correlation may exist between stroke and AD. Therefore, the participants in our trail may also suffer both AD and PSCI. And this will affect the evaluation of the outcome in this study. Potential spontaneous recovery at the early stage of stroke may have the confounding effects on this trial, but the waiting-list group can reduce the effects of it. Due to the limitations of equipment and capital, only part of the participants will get the fMRI scan. This may affect the generalizability of the results.

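### Secondary domains are named as efficacy targets and every two-sided P < .05 counts as significant, so one nominal result on FAQ, NPI or WHOQOL-BREF could be declared efficacy even if the primary outcome is negative

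*Protocol article*

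**What the plan says.** Four places in the protocol article bear on this.

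- **Objective (2.1).** The aim is to "evaluate the efficacy of acupuncture treatment on improving cognitive function, ADLs, mental state, and quality of life for PSCIND patients". Within that sentence the four domains are not ranked.
- **Discussion (8).** The length of intervention and follow-up is presented as a strength that "can provide reliable long-term effect evidence for acupuncture on improving cognitive function, mental state, and quality of life for PSCIND patients". Daily activities are not named there.
- **Outcome assessment (3.5 and Table 3).** The article states that "most primary and secondary outcomes will be measured at baseline, the end of intervention(12weeks), after an additional 12-week follow-up period (24 weeks"; a 36-week visit follows. FAQ, NPI and WHOQOL-BREF are scheduled at all three post-baseline visits, and no visit is singled out.
- **Statistical methods (7.5).** Groups are compared by analysis of variance, with Mann-Whitney U as the fallback. The threshold is then fixed: "Two-sided *P* < .05 represents statistical significance for all the analyses".

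The article does rank its outcomes. The Introduction says that "the primary aim of this study is to explore whether acupuncture can improve cognitive function of patients with PSCIND and reduce the chances" of progressing to dementia. Section 3.6 adds: "The primary outcome of this study is the cognitive function and incidence of PSD". The other scales come under the Secondary outcome heading, for example "We will use the Functional Activities Questionnaire (FAQ), which has a wide application to measure the IADLs" and "The 12-item version of neuropsychiatric inventory (NPI) will be used in this trial". The only sample size calculation is for MoCA.

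**The concern.** The ranking in sections 3.6 and 4 is not carried into the three places where it would limit a conclusion: the objective, the significance rule and the claim in section 8. Read together, these allow the following. Cognition and dementia incidence show no difference, one of the three secondary scales reaches P < .05 at one visit, and that result is significant under 7.5 and answers an efficacy objective under 2.1. With several scales, visits and arms in play, such a result is much likelier to arise by chance than the stated 5% suggests. At stake is whether the trial can support a statement that acupuncture improves daily activities, mental state or quality of life.

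**Working it through.** The article gives no error rate for the secondary scales, so there is no stated figure to reproduce. The check asks how often the stated rule gives a significant result when acupuncture has no effect.

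**Inputs from the article.** Three scales (sections 4.1-4.3), three post-baseline visits (3.5, Table 3), three arms in a 1:1:1 ratio (2.2), and two-sided 0.05 for every analysis (7.5).

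**Assumptions.** Each scale is tested separately at each visit; the article gives only the measurement times. Each scale yields one score. Correlations are not given, so a range is used: 0.3 to 0.7 between scales and 0.5 to 0.8 between visits.

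**Step 1: independent tests, as an upper reference.** One three-arm test per scale and visit makes 3 x 3 = 9 tests: 1 - 0.95^9 = 37%. At week 12 alone there are 3 tests: 1 - 0.95^3 = 14%.

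**Step 2: correlated tests.** Simulate standardised arm means Z with no true difference. Their correlation across scales and visits is the Kronecker product of two exchangeable matrices. For each scale and visit:

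- three-arm test: the sum over arms of (Z_arm - mean Z)^2, compared with the 95% point of chi-square on 2 degrees of freedom;
- contrast: (Z_acupuncture - Z_control)/√2, compared with 1.96, for sham and for waiting list.

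Chance of at least one event over the 9 scale-visit combinations:

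| Correlation (scales, visits) | Any three-arm P < .05 | Either acupuncture contrast, either direction | Either contrast, favouring acupuncture | Favouring acupuncture, after a significant three-arm test |
|---|---|---|---|---|
| 0.3, 0.5 | 32% | 51% | 27% | 14% |
| 0.5, 0.5 | 30% | 47% | 25% | 13% |
| 0.5, 0.7 | 27% | 42% | 22% | 12% |
| 0.7, 0.8 | 21% | 34% | 17% | 9% |

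At week 12 alone, any three-arm P < .05 has a chance of 11-14%. A result favouring acupuncture after a significant three-arm test has a chance of about 5%.

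**Step 3: cross-check with finite samples.** Using F and t tests with 95 patients per arm, correlations of (0.3, 0.6) and (0.5, 0.8) give 32% and 25% for any three-arm test. For an unprotected contrast favouring acupuncture they give 27% and 20%. This agrees with step 2.

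**Step 4: which column applies.** The harm is a false statement of benefit, so only the last two columns measure it. The comparator is 2.5%, the chance that one two-sided 0.05 test of one contrast falsely favours acupuncture. The last column fits analysis of variance followed by pairwise comparison. The column before it fits direct pairwise testing, which the Mann-Whitney fallback implies because it is a two-sample test.

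**The case against.** The strongest counter-argument is that handling of multiplicity for secondary outcomes is commonly left to a statistical analysis plan. That plan is not shown, and a journal article condenses the full protocol. Unadjusted secondary outcomes read as supportive are also ordinary practice. This stands to the extent that the absence of an adjustment, a testing order or a key visit is not itself a fault. It does not remove the point, because 7.5 fixes one threshold for every analysis, and 2.1 and 8 attach efficacy language to secondary domains.

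Three stronger readings are tempting, and the article does not support them.

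- *That there is no hierarchy.* There is one: the Introduction, section 3.6 and section 4 separate primary from secondary. What the article does not do is use that ranking in the significance rule.
- *That a chance finding would be reported as proven benefit.* This is a prediction. Section 2.1 speaks of evaluating, section 8 of what the design can provide, and section 10 commits to dissemination whatever the size or direction of effect. The text permits such a claim but does not announce it.
- *That a null trial has a 30% or 47% chance of a false benefit claim.* Those figures also count acupuncture appearing worse, and the 30% further counts differences between sham and waiting list. The relevant figures are about half or less.

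Testing at each visit is also an inference. It is a fair one, since a long-term claim in section 8 needs weeks 24 and 36, but the week-12 figures show what remains without it.

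**Conclusion.** The point holds in a limited form. The article ranks its outcomes, but its rule on significance ignores the ranking, while its objective and discussion treat secondary domains as matters on which efficacy will be shown. With no true effect, the chance of a false result favouring acupuncture on at least one of the three scales is about 17-27% with unprotected contrasts against either control. It is 9-14% when a significant three-arm test is required first, and about 5% when that route is confined to week 12. The nominal figure in that direction is 2.5%. These sizes rest on one score per scale, on the assumed correlations and, except at week 12, on separate testing at three visits. More than one score per scale, which the article neither states nor excludes for WHOQOL-BREF, would raise them. The primary analysis is not affected. What changes is which secondary conclusions the trial may draw.

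**What to change.** In 7.5, limit the P < .05 significance rule to the primary analysis. State there that FAQ, NPI and WHOQOL-BREF are supportive or exploratory, reported as estimates with 95% confidence intervals and without an efficacy claim. Reword 2.1 to follow the primary and secondary ranking already in sections 3.6 and 4. In section 8, drop the word *reliable* for mental state and quality of life.

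If the sponsor wants a confirmatory claim on these scales, one option is to test them only after a positive primary, at one visit and one contrast, with Holm adjustment over the three. This is not required. It would first need a settled decision rule for the primary, since sections 3.6-3.8 name several measures. Its cost in power can be bounded with Bonferroni, 0.05/3 = 0.0167. Assume a standardised effect equal to that planned for MoCA, 0.6/√((1.13^2 + 1.20^2)/2) = 0.6/1.1655 = 0.515. With 95 per arm, power per scale falls from 94% to 88%.

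The main fix costs a few sentences and needs no new patients, visits or data. The downside is that a nominally significant secondary result can no longer be called efficacy.

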### Trial design

2.2

This is a multicenter, single-blind, randomized controlled trail that participants will be random allocated to 3 groups with a 1:1:1 allocation ratio. The 3 groups are acupuncture group (AG), sham acupuncture group (NAG), and waiting-list group (WLG). The flowchart of the trial design is shown in Figure 1.

**Figure 1 F1:**
[figure not shown]
Flowchart of the trial design.

### Inclusion criteria

2.3

Patients are eligible for study inclusion if they

(1)Meet the diagnostic criteria of ischemic stroke^[18]^(2)Meet the diagnostic criteria of PSCIND^[7,19–21]^

(1)Have the ability to take care of themselves in daily life. Barthel index ≥60.(2)Montreal cognitive assessment scale (MoCA) < 26(3)Mini-mental State Examination (MMSE): MMSE Score >17 (illiteracy), or MMSE score > 20 (primary school culture), or MMSE score >24 (middle school and above);(4)Ischemic stroke within 6 months;(5)Men or women aged 18 to 75 years;(6)The patients sign informed consent and cooperate with the treatment.

### Exclusion criteria

2.4

Patients will be excluded if they have any one of the following:

(1)Patients were diagnosed as having cognitive impairment before cerebral infarction;(2)Patients were taking medications that may interfere in the efficacy assessment of the study therapies, including cholinesterase inhibitors, cytosolic sodium, or receiving acupuncture to treat cognitive impairment;(3)Patients who are unable to complete assessments during the screening process due to serious mental, cognitive, or emotional disorders;(4)Patients who have severe diseases in the internal organs, including the heart, liver, and kidney;(5)Patients live alone without long-term living partners or caregiver;(6)Women who are pregnant or preparing to pregnant or breast-feeding;(7)Patients who are recruited into other clinical trials which related to acupuncture or cognitive impairment within 1 month.

### Endpoint event

2.5

The patient meets the diagnostic criteria for dementia: MMSE score ≤17 (illiteracy), or MMSE score ≤ 20 (primary school culture), or MMSE score ≤24 (middle school and above).

### Withdrawal or dropout criteria

2.6

Participants will be terminated to continue this trial according to the following criteria:

(1)The participants who have a deteriorated condition or have had a serious adverse event;(2)The participants who suffer from certain complications or specific physiological changes during the study may not be appropriate to continue;(3)The participants who are unwilling to continue the study.

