### Incidence of PSD

3.8

We will use MMSE, which is the most widely used by frontline physicians, to detecting dementia. Dementia: MMSE score ≤17 (illiteracy), or MMSE score ≤20 (primary school culture), or MMSE score ≤24 (middle school and above).^[33]^

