## Ethics approval and consent to participate

9

The ethic committee of First Teaching Hospital of University of Traditional Chinese Medicine approved the study. We have also registered at ClinicalTrials.gov (http://www.chictr.org.cn/showprojen.aspx?proj=54764): ChiCTR2000033801. All patients gave their written informed consent before participating in the clinical trial. The details of our study, including trial objectives, characteristics, probable benefits and risks, other available treatment alternatives, and the subjects’ rights as well as obligations as stated in the Declaration of Helsinki, will be made clear to the patients by a study personnel who has their grouping code, and their agreement will be required. After obtaining the written informed consent, the subjects will be enrolled in the study. During the process of the trial, if new points regarding the study ethics emerge, written revisions regarding the informed consent will be handled by the Ethics Committee and, after their approval, the individuals’ consent will be requested again. In case of the patients’ withdrawal, their available data will be kept for the final analyses.

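### Section 2.6 ends trial participation for patients who deteriorate or have a serious event, so those affected between visits lose later primary-outcome assessments for reasons related to that outcome

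*Protocol article*

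**What the plan says.** Section 2.6 (Withdrawal or dropout criteria) opens with "Participants will be terminated to continue this trial according to the following criteria". Its first criterion is "The participants who have a deteriorated condition or have had a serious adverse event". The second covers complications or physiological changes that make continuing inappropriate, and the third covers unwillingness to go on. All three have the same consequence. The text does not distinguish stopping study treatment from leaving the study, does not define deterioration, and does not except cognitive decline.

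Section 3.6 states: "The primary outcome of this study is the cognitive function and incidence of PSD". Section 3.8 identifies PSD by MMSE cut-offs alone: "We will use MMSE, which is the most widely used by frontline physicians, to detecting dementia". Section 2.5 lists the same cut-offs as an endpoint event. Section 3.5 and Table 3 place MoCA, MMSE and CDR at baseline and weeks 12, 24 and 36, with none in between.

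For patients who withdraw, section 9 says that "their available data will be kept for the final analyses". No assessment after withdrawal is described.

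**The concern.** The Discussion presents the trial as the first randomised test of "preventing PSCIND progressing to PSD". Such progression is a deterioration, so the trigger for ending participation overlaps with the event the trial exists to count. If a patient worsens or has a serious event at week 5 and is terminated under 2.6, no week-12 MMSE is taken and the patient cannot be classified as PSD.

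The serious-event limb may act in the same way. The Introduction treats stroke recurrence and severity as what must be prevented to avoid PSD, and a recurrent stroke would plausibly be handled as a serious adverse event. Patients at high risk of conversion would then leave follow-up.

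At stake are the PSD count and the cognitive means in every comparison. Scores that were never taken cannot be recovered by any analysis plan, so this has to be settled in the protocol.

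**Working it through.** **The plan's own figure.** Section 7.5 needs 95 per group and assumes 20% dropout: 95 / (1 − 0.20) = 118.75, rounded up to 119; 119 × 3 = 357. The stated 357 is reproduced. The inflation replaces numbers lost. It assumes nothing about who is lost, so it does not correct selective loss.

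**What is lost and what is kept, from the text**
- Dementia or decline recorded at week 12, 24 or 36, then termination: that result is kept (section 9) and later visits are lost.
- Deterioration or a serious event between visits, then termination: the next and all later assessments are lost.
- No text calls for an assessment at termination, or says that a terminated patient counts as PSD.

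**Size for PSD.** The protocol gives no PSD rate at 36 weeks (the Introduction's 19.3% is a 10-year figure), so the risks and loss shares below are assumptions. Let p be the true risk and w the share of converters terminated before their MMSE and left out. Then

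observed risk = p(1 − w) / (1 − pw).

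*Same share lost in both arms; true risk 20% control, 10% acupuncture; 119 per arm less those lost; power two-sided at 0.05, normal approximation:*

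| w | control | acupuncture | difference (points) | power |
|---|---|---|---|---|
| 0 | 20.0% | 10.0% | 10.0 | 58% |
| 25% | 15.8% | 7.7% | 8.1 | 48% |
| 50% | 11.1% | 5.3% | 5.8 | 35% |
| 75% | 5.9% | 2.7% | 3.2 | 21% |

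For w = 50%: 0.20 × 0.5 / (1 − 0.10) = 0.111 and 0.10 × 0.5 / (1 − 0.05) = 0.053. The risk ratio hardly moves (0.10/0.20 = 0.50; 0.053/0.111 = 0.48), so the damage is to the absolute rates, their difference and power. With a true 10% vs 5%, the difference falls from 5.0 to 2.7 points at w = 50%.

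*Different shares lost, equal true risk of 15%:*
- 50% lost in acupuncture: 0.15 × 0.50 / (1 − 0.075) = 8.1%.
- 25% lost in control: 0.15 × 0.75 / (1 − 0.0375) = 11.7%.
- Shares exchanged: 11.7% in acupuncture vs 8.1% in control.

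The first pattern is a spurious benefit and the exchanged one a spurious harm.

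**Size for MoCA.** Inputs from section 7.5 are a difference of 0.6 and SDs of 1.13 and 1.20, giving a root-mean-square SD of √((1.13² + 1.20²)/2) = 1.166. Assume these describe normally distributed change, with mean 0.6 in acupuncture and 0 in control, and that patients falling below a threshold c are terminated. The mean of those remaining is μ + SD × φ(a) / (1 − Φ(a)), with a = (c − μ)/SD.

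| c | lost, acupuncture | lost, control | remaining difference |
|---|---|---|---|
| −2 | 1.3% | 4.3% | 0.53 |
| −1 | 8.5% | 19.5% | 0.40 |
| 0 | 30.3% | 50.0% | 0.26 |

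Under this mechanism the bias runs against acupuncture.

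**The case against.** Several points on the other side stand.

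**The loss is not total.** A reader might infer that dementia is removed before it can be counted at all. The documents do not support that: section 2.5 treats dementia as an endpoint event under its own heading, and section 9 retains available data. What is exposed is deterioration between visits, and every visit after termination.

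**The overlap is partly inferred.** Deterioration could mean general medical worsening only, and a serious adverse event is not defined. Table 3 records recurrence on a separate row from adverse events, to week 36, and section 6 speaks of adverse events of acupuncture. A recurrent stroke therefore need not trigger termination. This narrows the problem without removing it, because the wording as it stands permits the wider reading and excepts nothing. Section 3.4 sends all participants into follow-up, but it does not say that this includes patients terminated under 2.6.

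**The direction is not fixed.** A reader might infer a bias in favour of acupuncture, because needled patients are seen three times a week and their decline may be noticed sooner. That contact difference exists only in weeks 0 to 12. The acupuncture and sham arms share the same schedule, so it does not touch that comparison. Nothing says that needling visits screen cognition, and outcome assessors are masked (section 2.8). Unequal use of a discretionary rule remains possible, since acupuncturists and waiting-list patients are unblinded, but it could go either way.

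**The shares lost are assumed.** Nothing in the protocol supports one set of shares over another, which is why ranges and the reverse pattern are shown.

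**Conclusion.** The concern holds in this form. As written, section 2.6 ends outcome assessment for patients selected by a criterion that can overlap with the primary outcome, and section 9 provides for nothing afterwards. If those terminated between visits are more likely to convert than those who stay, PSD incidence is understated. Similar loss in the arms shrinks the difference: 10.0 to 5.8 points at 50% loss, on an assumed 20% vs 10%. Unequal loss can produce a false benefit or a false harm: 8.1% vs 11.7% or the reverse, on an assumed equal 15%.

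The mechanism rests on the text; the sizes rest on assumed rates. If deterioration was meant to exclude cognitive decline, and recurrence to lie outside the serious-event limb, the effect would be smaller. The protocol says neither.

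**What to change.** Reconcile sections 2.5, 2.6, 3.8 and 9 so that:
- the deterioration in criterion 1 is defined, and stopping study treatment is stated separately from ending outcome assessment. Whether treatment stops is left to the clinicians;
- criteria 1 and 2 do not end outcome follow-up. These patients keep the MoCA, MMSE and CDR already scheduled at weeks 12, 24 and 36;
- they are analysed in their allocated arm, and the text says how they enter the PSD count;
- only withdrawal of consent to follow-up ends data collection.

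An extra MMSE or CDR triggered by the event is not advised. It would be an unscheduled assessment and could make detection of PSD unequal between arms.

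The cost is a short amendment and the already scheduled visits for a few more patients. It should be in place before patients are terminated under 2.6, because assessments missed cannot be recovered.
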